#### Primary analysis

The primary endpoint is BMI reduction and the improvement/stabilization of measures of subclinical CVD. Additionally, we will examine changes in anthropometric indices (waist circumference, waist to hip ratio, and percentage of body fat), metabolic parameters, conventional/advanced lipid testing, inflammatory marker panel, systolic and diastolic blood pressure, dietary and physical activity scores, coronary artery calcification, carotid intima-media thickness, and endothelial function. The primary null hypothesis is that no difference exists between the treatment groups in the outcomes measured.

Analysis will be conducted using the intention-to-treat principle; that is, all subjects who were randomized will be included in the data analysis regardless of completion of the study status. Continuous variables (e.g., age and biochemical variables) will be assessed for normality by examining graphically and by statistical methods. Categorical variables will be described using frequency distributions, whereas continuous variables will be described using means and standard deviations for normally distributed variables, and median (interquartile range) for non-normally distributed variables. Differences relating to study-arm assignment in these variables between groups will be evaluated using chi-square tests for categorical variables and independent t-tests for continuous variables.

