### Study objectives

The primary purpose of BEHHS is to assess if the addition of a personalized, interactive, web-based, diet and lifestyle-counselling system to an existing web-based wellness engine will reduce/stabilize components of the metabolic syndrome and markers of subclinical CVD in an employee population. Primarily, this addition is hypothesized to result in improvement of subclinical markers of cardiovascular disease as a direct impact of expected weight loss in the intervention arm versus the control arm.

The secondary purpose of BEHHS is to determine if the addition of a personalized web-based engine results in a greater adoption of healthy behaviors (including dietary habits, sleep habits, and physical activity levels) compared to a nonpersonalized wellness engine.

Third, the study aims to assess if the addition of a personalized web-based engine to an existing platform results in stabilization of subclinical atherosclerotic disease progression in high-risk patients.

Fourth, the study aims to document the natural history of atherosclerotic disease (as assessed by coronary artery calcification, carotid intima-media thickness, and peripheral artery tonometry) in a high-risk employee population.

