### Statistical analysis

#### Sample size calculations

Our hypothesis is that the addition of a personalized, interactive, web-based diet and lifestyle counselling system to an existing, web-based, wellness engine will reduce/stabilize components of the MetS, so differences in values of components of the MetS and markers of subclinical CVD (CVD is not apparent at baseline), will be observed on follow-up visits at 4, 8, and 12 months.

A two-by-two repeated measures design consists of two groups of subjects, each measured at two time points. In this case, the primary goal of the study is to compare the change of weight across time in group 1 to the change across time in group 2. Sample sizes of 85 in group 1 and 85 in group 2 achieve 80 % power to detect a difference in mean weight changes of 5.8 lbs. with a standard deviation of 10.0 lbs. at the first time point, a standard deviation of 10.0 lbs. at the second time point, and a correlation between measurement pairs of 0.100. The significance level (alpha) is 0.05 using a two-sided, two-sample t-test.

Group sample sizes of 85 and 85 achieve 80 % power to detect a difference in BMI of 1.019 kg/m^2^, 1.359 kg/m^2^, or 1.699 kg/m^2^ in a design with four repeated measurements and having a compound symmetry covariance structure when the standard deviation is 3, 4, or 5, the correlation between observations on the same subject is 0.500, and the alpha level is 0.050.

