### Limitations

A major limitation of the study is the lack of blinding of study subjects, which is not possible due to the obvious nature of the intervention. This study has a small sample size, which may prove underpowered to achieve secondary objectives.

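### The primary outcome is stated in three conflicting ways, with no rule for what makes the trial positive and power calculations for only two of the candidates (weight and BMI)

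*Protocol article*

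**What the plan says.** The protocol article gives three descriptions of what is primary.

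- **Sample size calculations:** "the primary goal of the study is to compare the change of weight across time in group 1", against the same change in group 2. This is sized with two time points and a two-sample t-test.
- **Primary analysis:** "The primary endpoint is BMI reduction and the improvement/stabilization of measures of subclinical CVD". The subclinical measures are not listed in that sentence. Coronary calcium, carotid intima-media thickness (cIMT) and endothelial function then appear in the next sentence, among the further outcomes to be examined.
- **Study objectives:** the primary purpose is to learn whether the added program "will reduce/stabilize components of the metabolic syndrome and markers of subclinical CVD in an employee population". The hypothesis that opens the Sample size section agrees with this: "differences in values of components of the MetS and markers of subclinical CVD (CVD is not apparent at baseline), will be observed on follow-up visits".

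The levels also overlap. The third aim in the Study objectives asks whether the program "results in stabilization of subclinical atherosclerotic disease progression in high-risk patients", although subclinical disease is already in the primary purpose and the primary endpoint.

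The Primary analysis section then states: "The primary null hypothesis is that no difference exists between the treatment groups in the outcomes measured". It does not say which results, or how many, would make the trial positive.

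A level of 0.05 is written for the weight calculation (two-sided) and for the BMI calculation. No level and no power calculation are given for the subclinical measures or the MetS components.

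**The concern.** A statistician writing the analysis plan could not tell from this text which outcome carries the primary test. The conflict is in the printed text, so it is not a detail that the article has merely left to another document.

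Two things are at stake. First, the primary result could be chosen after the data are seen, from among outcomes that the protocol has each called primary. Second, the operating characteristics are undefined. A null that spans all measured outcomes can be read as rejected by any one of them, which raises the type I error. The word joining BMI and the subclinical measures can instead be read as requiring both, which lowers power. The stated 80% covers neither reading.

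**Working it through.** **Inputs from the Sample size section.** 85 per group. Weight: difference 5.8 lb, SD 10.0 lb at each time point, correlation 0.1, two-sided alpha 0.05. BMI: differences 1.019, 1.359 and 1.699 kg/m² for SD 3, 4 and 5, four measurements, compound symmetry, correlation 0.5, alpha 0.05 (taken as two-sided).

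**1. Reproducing the weight figure.**
- SD of change = √(10² + 10² − 2 × 0.1 × 10 × 10) = √180 = 13.42 lb.
- SE of the difference = 13.42 × √(2/85) = 2.058.
- 5.8/2.058 = 2.818, and power = Φ(2.818 − 1.960) = 80.5% (80.0% with the noncentral t).

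The stated figure is reproduced.

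**2. Reproducing the BMI figure.** It is reproduced as a comparison of the mean of four measurements.
- SD of the mean for SD 3 = 3 × √((1 + 3 × 0.5)/4) = 2.372.
- SE = 2.372 × √(2/85) = 0.364.
- 1.019/0.364 = 2.801, and power = Φ(2.801 − 1.960) = 80.0% (79.5% with the noncentral t).

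SD 4 and SD 5 give the same power. So 85 per group was justified twice, for two different primaries, each time at the full 0.05.

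**3. BMI as a change between two visits.** Same SD, difference and correlation.
- SD of change = 3 × √(2 × (1 − 0.5)) = 3.0.
- SE = 3.0 × √(2/85) = 0.460.
- 1.019/0.460 = 2.214, and power = Φ(2.214 − 1.960) = 60%.

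The other two SDs also give 60%. The stated BMI calculation therefore does not support a two-visit BMI reduction at 80%.

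**4. If any one result at 0.05 suffices.** The counts are assumptions drawn from the document: four subclinical measures (coronary calcium, cIMT, reactive hyperemia index, augmentation index) and the five MetS components in the Inclusion criteria. Counting the augmentation index as a primary measure is itself an inference, because the article ties it to arterial stiffness and not to endothelial function. For independent tests the chance of at least one false positive is 1 − 0.95^k. The correlated values are simulated two-sided z-tests.

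| Outcomes counted | k | Independent | Correlated |
|---|---|---|---|
| Weight, BMI | 2 | 9.75% | 6.5% (correlation 0.95) |
| BMI + 4 subclinical | 5 | 22.6% | 21% (0.3), 18% (0.5) |
| Weight, BMI + 4 subclinical | 6 | 26.5% | 22% (0.3), 19% (0.5)* |
| The same 6 + 5 MetS components | 11 | 43.1% | 36% (0.3), 29% (0.5)* |

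*Weight–BMI correlation 0.95; all other pairs as shown.

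**5. If all must succeed.** Type I error does not exceed 5%. Suppose, generously, that BMI and each of the four subclinical measures had 80% power. Joint power would be 0.8^5 = 33% if independent, 44% at correlation 0.3 and 51% at 0.5. The true power of the subclinical measures is unknown, because the document gives no calculation for them.

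**The case against.** Several points on the other side are fair.

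- **Alpha.** It would be easy to say that every outcome is tested at 0.05. The article gives that level only for weight and BMI. Extending it to the rest is an inference from the absence of any other level.
- **Success rule.** A reader might infer that the trial-wise error is certainly far above 5%. The document does not establish this. The inflation needs the any-one-suffices reading. The wording of the null permits that reading, but the joint wording of the endpoint points the other way.
- **Weight and BMI.** These are nearly the same measure in adults, and the Study objectives expect subclinical improvement to follow from weight loss. That pair alone adds little (6.5% at correlation 0.95). The real conflict is between weight or BMI and the subclinical and MetS outcomes.
- **Larger outcome counts.** One might count everything measured and quote a larger error. Most of those measures are introduced as additional, so the text does not support treating them all as primary.
- **Stabilization.** A reader might infer that an unchanged marker in the intervention arm would count as success. No rule says so. The only stated null is between arms, so stabilization would be judged against control. The wording is loose, but it is not a route to success by default.
- **Repeated visits.** The BMI calculation with four measurements suggests one overall comparison, so a separate test at each visit should not be assumed.
- **Limitations section.** It warns "This study has a small sample size, which may prove underpowered to achieve secondary objectives". This is a disclosed limitation and is not evidence of conflicting primaries.

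These points narrow the claim about error. They do not resolve which outcome is primary.

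**Conclusion.** The concern holds as a contradiction within the document. Weight change, BMI with unlisted subclinical measures, and MetS components with subclinical markers are each presented as primary. Subclinical stabilization is placed at two levels, and no success rule connects them. Only weight and BMI have a power calculation.

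The consequence depends on a rule that the document does not state:

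- **Any one result at 0.05 suffices:** the false-positive chance is about 23% for five outcomes (21% at correlation 0.3) and about 29% to 43% for eleven.
- **All must succeed:** alpha is not inflated, but power falls below the stated 80%, to roughly 33% to 51% for five outcomes even if each had 80% on its own.

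The outcome counts, the correlations and the 0.05 level for outcomes other than weight and BMI are assumptions. The contradiction itself rests on none of them. It should be settled before analysis, because it determines which result the trial stands on.

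**What to change.** Name one primary outcome that matches a stated power calculation, and test it alone at two-sided 0.05.

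- **Simplest choice:** the between-arm difference in weight change from baseline to one named follow-up visit, for example 12 months. This fits the existing calculation (5.8 lb, 85 per group, 80%).
- **If BMI is preferred:** either keep the four-measurement comparison that was powered, or restate the power for a two-visit change. That is about 60% at 85 per group under the stated inputs. Restoring 80% for a difference of 1.019 at SD 3 would need 2 × (3 × 2.802/1.019)² = 136.1, so 137 per group before dropout.
- **Everything else named as primary:** make the subclinical measures and MetS components secondary, itemise them, and test them in a fixed order or with Holm adjustment.
- **Wording:** define the endpoint as a between-arm difference in change instead of improvement or stabilization, limit the primary null to the one named outcome, and align the Study objectives, Sample size calculations and Primary analysis sections.

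With weight as the primary outcome, the cost is wording in those three sections and no extra participants. By contrast, keeping several primaries under a Bonferroni split would need about 102 to 103 per group for two tests, 130 to 132 for six and 145 to 147 for eleven, before dropout. The downside is that the sponsor could no longer claim primary success on subclinical markers alone, and that the stated BMI power becomes less favourable if a two-visit BMI change is chosen.

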## Methods/design

### Study design

The Baptist Employee Healthy Heart Study is a prospective, randomized, nonblinded study. The study sample will consist of approximately 200 male and female BHSF employees meeting the inclusion/exclusion criteria for the study. The participants will be randomized into two groups: the intervention arm, Group 1, or the control arm, Group 2 (Fig. 1).

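### The intention-to-treat promise covers everyone randomized, but the t-tests named, run as written, give an available-case comparison that also ignores the intermediate visits and the repeated-measures design used to size BMI

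*Protocol article*

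**What the plan says.** All references are to the protocol article.

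- **Population.** Primary analysis adopts intention-to-treat and defines it in working terms: "all subjects who were randomized will be included in the data analysis regardless of completion of the study status".
- **Test.** The same section says that differences by study arm "will be evaluated using chi-square tests for categorical variables and independent t-tests for continuous variables". It names no other between-arm method. The variables meant are introduced two sentences earlier: "Continuous variables (e.g., age and biochemical variables) will be assessed for normality".
- **Endpoint.** "The primary endpoint is BMI reduction and the improvement/stabilization of measures of subclinical CVD".
- **Weight sizing.** Sample size calculations gives the primary goal as to "compare the change of weight across time in group 1 to the change across time in group 2", with two time points and a two-sided two-sample t-test. "Sample sizes of 85 in group 1 and 85 in group 2" are said to give 80% power for 5.8 lb.
- **BMI sizing.** The next paragraph sizes BMI differently, on four repeated measurements with compound symmetry and a correlation of 0.5.
- **Enrolment and visits.** Study design plans for "approximately 200 male and female BHSF employees". Table 1 schedules weight and height at enrollment and at months 4, 8 and 12.

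**The concern.** A t-test of change, or of a follow-up value, needs that follow-up value. A randomized subject without it cannot enter the test unless the value is imputed. Once anyone is lost, the promised population and the named test therefore do not fit together, and the article does not say how they are to be reconciled.

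Two further losses follow. A two-time-point test makes no use of the intermediate weights, including those of people who attend month 4 or month 8 and then leave. It also makes no use of baseline as a covariate, although baseline is measured in everyone.

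At stake is a result labelled intention-to-treat but estimated only in those who were measured. The trial is not blinded, and use of the intervention tools is optional (Description of the intervention program). Attendance that depends on weight and differs by arm is therefore plausible, though nothing in the article shows that it will occur.

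**Working it through.** **1. The plan's own figures reproduce.**

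Weight: SD 10.0 lb at both times, correlation 0.100.
- SD of change = √(10² + 10² − 2 × 0.1 × 10 × 10) = √180 = 13.42 lb.
- With 85 per arm and a difference of 5.8 lb, two-sided alpha 0.05, power is 80.0% (noncentral t), as stated.

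BMI: correlation 0.5, four measurements.
- SD of the mean of four = SD × √((1 + 3 × 0.5)/4) = 0.791 × SD.
- With 85 per arm, power for 1.019, 1.359 and 1.699 kg/m² at SD 3, 4 and 5 is 80.0% (normal approximation) or 79.5 to 79.6% (noncentral t).

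Both calculations are sound on their own terms. The BMI figure, however, belongs to an analysis that uses all four measurements.

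**2. The BMI sizing does not match a t-test of change.**

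For a two-point change at correlation 0.5, SD of change = SD × √(2 × (1 − 0.5)) = SD. With 85 per arm and the same differences, power is 60.0% (normal approximation), not 80%.

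**3. What baseline adjustment is worth.**

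Change-score variance is 2σ²(1 − ρ); baseline-adjusted variance at one visit is σ²(1 − ρ²). Their ratio is (1 + ρ)/2.
- BMI, ρ = 0.5: ratio 0.75, about 25% lower variance.
- Weight, ρ = 0.1: ratio 0.55, about 45% lower variance.

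**4. What the enrolment margin covers.**

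1 − 170/200 = 15%. The article neither states a dropout rate nor links these two numbers, so 15% is an inference. Assuming 100 randomized per arm and equal loss, power of the weight t-test for 5.8 lb is:

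| Assumed loss | Observed per arm | Power |
|---|---|---|
| 0% | 100 | 86.0% |
| 10% | 90 | 82.2% |
| 15% | 85 | 80.0% |
| 20% | 80 | 77.6% |
| 30% | 70 | 71.9% |

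Power is protected up to about 15% loss. Enrolling extra people does nothing about bias.

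**5. Illustrations of bias (all inputs assumed).**

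*(a)* Observed subjects differ by 5.8 lb, intervention dropouts gain no benefit, and control dropouts resemble the observed controls. The effect in all randomized is 5.8 × (1 − d), where d is intervention dropout.
- d = 15%: 4.93 lb; the observed estimate is 5.8/4.93 = 1.18 times as large.
- d = 25%: 4.35 lb; 5.8/4.35 = 1.33 times as large.

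*(b)* Dropouts in one arm differ from stayers by 5 lb in mean change, in either direction. The observed mean for that arm shifts by 5 × d: 0.50 lb at 10%, 0.75 lb at 15% and 1.5 lb at 30% (9%, 13% and 26% of 5.8 lb).

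**The case against.** The strongest reply is that this is only an absent missing-data rule, which an article commonly leaves to the full protocol or analysis plan. A t-test on imputed values would be compatible with including everyone. That is right as far as it goes, and the lack of an imputation rule is not the point here. The point is that the article does fix a test, and that this test fits neither the stated population without a further step nor the design used to size BMI.

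A second reply is that the t-test sentence may be descriptive, since its examples include age. That reading is possible. But the sentence stands under Primary analysis, its examples also include biochemical variables, which are outcomes, and the only other test named for weight change is again a two-sample t-test. That second mention is in a power calculation, which is not itself an analysis commitment.

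A third reply is that the four-measurement BMI calculation already points to a repeated-measures analysis. It does, and it supports the change proposed. The analysis section never names such a model.

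A reader might infer more: that the result will be a completers analysis, that about 30 people will be dropped, or that the estimate will favour the program. The documents support none of these. Nothing says that subjects without follow-up are excluded. A t-test at a given visit uses whoever attended it, which need not be the study completers. No dropout rate is stated. Who leaves, and from which arm, is conjecture.

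**Conclusion.** The point holds as a mismatch between the stated population and the named test. Run as written and without imputation, the t-test is an available-case analysis that omits randomized subjects lacking the follow-up value, leaves intermediate visits and baseline adjustment unused, and departs from the BMI sizing design.

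The efficiency loss can be sized from the plan's own correlations: the change-score t-test gives up a variance reduction of about 25% for BMI and 45% for weight. The bias cannot be sized. The 4.93 lb and 4.35 lb figures rest wholly on assumed intervention dropout of 15% and 25% with no benefit in dropouts, and the direction is unknown.

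The change is worth making because it is cheap and brings analysis, population and sizing into line. It does not call the trial's design into question.

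**What to change.** - **Primary BMI/weight analysis:** a repeated-measures mixed model using all month 4, 8 and 12 values, with arm-by-visit and baseline-by-visit terms, and the month 12 contrast between arms as the primary estimate.
- **Sensitivity analysis:** one control-based imputation analysis that includes every randomized subject. It is needed for two reasons. The mixed model assumes data are missing at random; if intervention dropouts had no follow-up values and no benefit, it too would return about 5.8 lb in illustration (a). And with baseline as a covariate, the model takes in only subjects with at least one follow-up value.
- **Labelling:** describe any retained t-test as available-case, and say whether the present t-test sentence is meant for baseline description or for outcomes.
- **Sizing text:** state the power for the month 12 contrast, since the present BMI figure reproduces as a comparison of the average over four measurements. On the plan's inputs, a baseline-adjusted single-visit BMI comparison has SD × √(1 − 0.5²) = 0.866 × SD. With 85 per arm this gives about 72.5% power for the stated differences (normal approximation), against 60.0% for the change score.

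The cost is analysis text and modest programming. All the measurements are already scheduled.

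### The only between-arm test named for continuous outcomes is an unadjusted t-test, at best on change from baseline; it gives up precision and does not match the model used to size BMI.

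*Protocol article*

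**What the plan says.** All references are to the protocol article.

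- **Primary analysis, endpoint:** "The primary endpoint is BMI reduction and the improvement/stabilization of measures of subclinical CVD". The other outcomes follow as changes: "Additionally, we will examine changes in anthropometric indices", and then a list that includes lipids, blood pressure, coronary calcium, carotid thickness and endothelial function.
- **Primary analysis, test:** arm differences are to be tested with "chi-square tests for categorical variables and independent t-tests for continuous variables". The variables meant are the continuous and categorical ones just described, with age and biochemical measures as examples.
- **Sample size calculations, weight:** the aim is to "compare the change of weight across time in group 1 to the change across time in group 2". With 85 per arm, power is put at 80% for "a difference in mean weight changes of 5.8 lbs", with an SD of 10 lb at each of two time points and a correlation of 0.1. The test is given as follows: "The significance level (alpha) is 0.05 using a two-sided, two-sample t-test".
- **Sample size calculations, BMI:** 85 per arm gives 80% power for differences of 1.019, 1.359 or 1.699 kg/m² (SD 3, 4 or 5), with four measurements per person, compound symmetry and a correlation of 0.5.
- **Study procedures and Table 1:** anthropometry is taken at all four visits. Blood tests, EndoPAT and carotid ultrasound are done at visits 1, 2 and 4.

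**The concern.** In a randomized trial with a baseline measurement of the outcome, there are three simple ways to compare arms: on the follow-up value, on the change, or on the follow-up value with baseline as a covariate. The third is asymptotically never less precise than the other two. How much it gains depends on the correlation between baseline and follow-up. A change score does poorly when that correlation is low, and a follow-up comparison does poorly when it is high. The article names only an unadjusted test, and for weight it pairs a change score with an assumed correlation of 0.1, where subtraction is least efficient.

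The second issue is consistency. The power claimed for BMI, the named primary endpoint, comes from a four-measurement design. The analysis section describes no analysis of that kind. If BMI is in fact tested at a single visit with a t-test, the stated power does not apply.

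**Working it through.** **Weight: reproduce the plan's figure.** Inputs: SD 10 and 10 lb, correlation r = 0.1, 85 per arm, two-sided alpha 0.05, difference 5.8 lb.

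- SD of change = √(10² + 10² − 2 × 0.1 × 10 × 10) = √180 = 13.42 lb.
- Power at 85 per arm = 80.0% (noncentral t; 80.5% by the normal approximation). The stated figure is reproduced as a t-test on change.
- A t-test on follow-up weight alone (SD 10) would have needed only 47 per arm, so the 85 does not come from an analysis without baseline.

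**Weight: condition on baseline.**

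- Residual SD = 10 × √(1 − 0.1²) = 9.95 lb.
- Variance relative to change = (1 − r²) / [2(1 − r)] = (1 + r)/2 = 0.55.
- Power at 5.8 lb with 85 per arm = 96.6%; alternatively, 80% power needs 47 per arm. The difference detectable with 80% power at 85 per arm falls from 5.8 to 4.3 lb.

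**BMI: reproduce the plan's figures.** The variance of the mean of four measurements under compound symmetry with r = 0.5 is SD² × (1 + 3 × 0.5)/4 = 0.625 SD². With SD 4, the detectable difference is (1.960 + 0.842) × 4 × √0.625 × √(2/85) = 1.359 kg/m². SD 3 and SD 5 give 1.019 and 1.699. All three stated values are reproduced.

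**BMI: power of analyses the trial might run**, at the stated differences, 85 per arm, r = 0.5, normal approximation. The results are the same to within rounding for SD 3, 4 and 5.

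| Analysis | Variance (× SD²) | Power |
|---|---|---|
| Mean of four measurements (the sizing model) | 0.625 | 80.0% |
| One visit, t-test on follow-up value | 1.00 | 60% |
| One visit, t-test on change: 2(1 − 0.5) | 1.00 | 60% |
| One visit, baseline as covariate: 1 − 0.5² | 0.75 | 72.5% |
| Mean of three follow-ups, unadjusted or as change | 0.667 | 77.4% |
| Mean of three follow-ups, baseline as covariate: 0.667 − 0.25 | 0.417 | 92.9% |

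**Sensitivity to the correlation.** Values above 0.5 are assumptions; the article does not give them.

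| r | ANCOVA variance / change-score variance | ANCOVA variance / follow-up-only variance |
|---|---|---|
| 0.1 (plan, weight) | 0.55 | 0.99 |
| 0.5 (plan, BMI) | 0.75 | 0.75 |
| 0.7 | 0.85 | 0.51 |
| 0.8 | 0.90 | 0.36 |
| 0.9 | 0.95 | 0.19 |

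**Chance imbalance.** The standard error of the baseline weight difference is 10 × √(2/85) = 1.53 lb. At r = 0.1, a change score subtracts the whole imbalance where one tenth would be right. An imbalance of one standard error therefore shifts the estimate by 0.9 × 1.53 = 1.4 lb, against a target of 5.8 lb. This shift averages to zero over randomizations and is already counted in the SD of 13.42. It is where the excess variance comes from, not an addition to it.

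**The case against.** A reader might infer that the t-tests ignore the baseline value of every outcome. The article does not support that. Weight is compared as change, the primary endpoint is a reduction in BMI, the further outcomes are to be examined as changes, and the 85 per arm is reproduced on change scores. Baseline is subtracted, not ignored. For the same reason, the roughly five-fold variance penalty that a follow-up-only test would carry at a correlation of 0.9 should not be charged to this plan.

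The test sentence may also describe baseline characteristics, since age is one of its examples. On that reading the outcome model is simply not printed, and a condensed article may leave it to an analysis plan that is not shown. That objection has weight. Against it, the sentence stands under the primary analysis heading, follows the intention-to-treat statement, and is the only between-arm method given there. The weight calculation separately names a two-sample t-test on change. On the narrower reading, the efficiency point still holds for weight.

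The large gain for weight also rests on the plan's correlation of 0.1. If that input is too low, the gain over a change score shrinks, to about 5% of variance at 0.9. This stands, and it limits the size of the point. Finally, one linear form for all outcomes would be too broad, because some, such as coronary calcium, may be skewed and the plan itself intends normality checks.

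**Conclusion.** The point holds as one of efficiency and consistency. The named test does not condition on baseline values that the trial collects anyway. On the plan's own inputs, this leaves a variance ratio of 0.55 for weight and 0.75 for BMI at one follow-up visit. The corresponding power is 80% against about 97% for weight, and about 60% against about 72% for BMI. The BMI power of 80% belongs to a four-measurement model that the analysis section does not describe.

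These sizes assume the stated SDs and correlations, equal variances over time, 85 analysed per arm, and outcomes suited to a linear model. With a true correlation near 0.9, the gain over a change score would be small.

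A reader might also infer that the planned comparison is biased, or that the weight comparison is underpowered. Neither follows. Randomization keeps a change-score comparison unbiased, and the weight calculation delivers its 80% with the test it names.

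**What to change.** State the primary BMI analysis as a linear model with arm and baseline BMI, either at month 12 or as a repeated-measures model over months 4, 8 and 12. Say which, and make the BMI power statement refer to that same model. Adjust each other continuous outcome for its own baseline value, with a transformation or another model where the distribution is skewed, as it may be for coronary calcium. State which variables the t-test and chi-square sentence covers.

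For coronary calcium, scanned only in those over 35, confirm when the baseline scan takes place relative to allocation. The abstract puts it at visit 1, but Table 1 lists only a referral there, and the allocation envelope is opened on the visit day.

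The cost is a few sentences of analysis text, a rerun of the BMI calculation and minor programming. No new data are needed.
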